### Safety monitoring

3.5

An independent data safety management board (DSMB) will oversee the safety aspects of this study. The DSMB will also include independent specialist physicians from different medical subspecialties. The DSMB will periodically examine the safety data emerging from the study and provide its recommendations to the chief investigator (CI) who will then pass these onto the independent ethics committee (IEC). The roles and responsibilities of the DSMB, their operational procedures, and method of communication with the CI will be described in a separate DSMB charter. Members of DSMB will not be investigators in the study nor will they have any conflict of interest with the CI.

The clinical trial may be prematurely suspended or terminated if, in the opinion of the DSMB or PIs, there is reasonable cause. Written notification, documenting the reason for study suspension or termination, will be provided by the suspending or terminating party. The pertinent regulatory authorities will be informed according to the national regulations.

Circumstances that may warrant termination include:

Determination of unexpected, significant, or unacceptable risk to patients.Insufficient adherence to protocol requirements.Data that are not sufficiently complete and/or evaluable.Plans to modify, suspend, or discontinue the development of the IP.

If the study is prematurely terminated or suspended, the CI will promptly inform the site-specific PIs, their institutions, and the regulatory authority of the termination or suspension and the reason(s) for the termination or suspension. The IEC will also be informed promptly and provided the reason(s) for the termination or suspension by the Sponsor or by the CI/institution, as specified by the applicable regulatory requirement(s).

Patients will be free to withdraw from the study at any time for any reason without penalty to their continuing medical care. In addition, patients must be withdrawn from the study by the site PI in consultation with the CI for the following reasons:

Grade 4 clinical adverse events considered causally related to Tecfidera.Allergic or anaphylactic reactions to IP.Development of severe lymphopenia (persistent lymphocyte count <0.5×10^9^ cells/L, for 8 weeks).Pregnancy.Compliance failure.Protocol violation.Serum creatinine >1.2 × upper limit of normal (ULN).Alanine aminotransferase (ALT) >5 × ULN.Single aspartate aminotransferase (AST) >8 × ULN.The ALT or AST levels >3 × ULN for 4 consecutive weeks.ALT or AST >3 × ULN and (total bilirubin >2 × ULN).ALT or AST >3 × ULN with appearance of fatigue, nausea, vomiting, right upper quadrant pain or tenderness, fever, rash, and/or eosinophilia (>5%).

Every effort will be made to ensure that patients who do not complete all study requirements return to the site for the Early Termination Visit, 4 weeks after the last dose of IP. Patients who withdraw due to an AE or SAE will be given appropriate care under medical supervision until the symptoms resolve or the patient's condition becomes stable.

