After completing Week 36 procedures, all patients will return to the study site at Week 40 for the End of Study Visit (4 weeks after the end of treatment visit). Patients who discontinue the study early will be asked to return to the study site for the early termination procedures 4 weeks after their last dose of Tecfidera/placebo. At this visit, neurological and physical examination will be performed and vital signs (blood pressure, pulse, temperature, and respiratory rate) will be recorded. The visit will also involve an assessment of ALSFRS-R, NPI and SI, FVC as measured by handheld spirometer, SNIP test, quantitative hand muscle testing by dynamometry, and global strength using MRC score. All patients will undergo laboratory evaluation of hematological and biochemical parameters as well as urinalysis. Urine will also be collected to test neurotrophin receptor P75 levels (secondary endpoint). An ALSSQOL-R questionnaire will also be completed by all patients. Adverse events and changes to concomitant medications will be observed and evaluated.

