### Statistical methods

3.6

The statistical analysis will be performed using statistical analysis system (SAS) Version 9.4. All details regarding the statistical analysis and the preparation of tables, listings, and figures will be described in the Statistical Analysis Plan (SAP) and approved by the Sponsor before database lock. The default summary statistics for continuous variables include number of contributing observations (n), mean, SD, median, minimum, and maximum. For categorical variables, the number and percentage (in each category will be the default summary presentation. “Baseline” is defined as the last observed value of the parameter of interest prior to the first intake of IP (this includes unscheduled visits). For numerical variables, change from Baseline will be calculated as the difference between the value of interest and the corresponding Baseline value. All formal statistical tests will be two-sided at the 5% significance level. Point estimates of treatment differences will be accompanied with a two-sided 95% confidence intervals. In the case of normality assumption violations, appropriate non-parametric methods will be used for analysis. All data will be presented in by-patient listings.

The following analysis populations will be defined as follows:

i.*Intent-to-Treat (ITT) Population*- The ITT population will include all randomized patients. In this population, treatment will be assigned based upon the treatment arm to which patients were randomized regardless of which treatment they received;ii.*Safety Population (SAF)*- The SAF includes patients who are randomized and took at least 1 dose of the IP. The safety analysis will be conducted according to the treatment that a patient actually receives;iii.*Per Protocol Population (PP)-* The PP population will include all patients who do not have major protocol deviations that would affect the evaluation of the primary efficacy endpoint.

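### Mandatory withdrawal from the study, not only from study drug, means the Week 36 ALSFRS-R is generally not collected for some randomised patients, which conflicts with an all-randomised comparison

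*Protocol article*

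**What the plan says.** Section 3.5 (Safety monitoring) lists reasons for which "patients must be withdrawn from the study by the site PI in consultation with the CI for the following reasons". The object of withdrawal is the study, not the study drug. The list contains:

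- events tied to the drug, for example "Grade 4 clinical adverse events considered causally related to Tecfidera" and allergic reactions to the product;
- laboratory thresholds, for example "Development of severe lymphopenia (persistent lymphocyte count <0.5×10^9^ cells/L, for 8 weeks"), and limits for creatinine, ALT and AST;
- reasons that are not toxicity: pregnancy, and "Compliance failure.Protocol violation".

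Two places describe what follows. Section 3.4 (End of Study) says: "Patients who discontinue the study early will be asked to return to the study site for the early termination procedures 4 weeks after their last" (that is, the final intake of active drug or placebo). Section 3.5 repeats that every effort will be made to have non-completers "return to the site for the Early Termination Visit, 4 weeks after the last dose of IP". ALSFRS-R is among the assessments at that visit. Nothing in the article keeps these patients on the Week 12, 24 and 36 schedule. The continuing attention promised to those who withdraw for an adverse event is medical care, not outcome assessment.

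Section 3.6 (Statistical methods) says: "The ITT population will include all randomized patients", analysed by randomised arm whatever treatment they received. Section 2.2 puts the primary comparison at Week 36, and section 3.6 analyses it with a mixed model for repeated measures. Missing-data handling is left to the SAP.

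**The concern.** The article treats stopping the drug and leaving the study as one event. A comparison of all randomised patients at Week 36 needs a Week 36 value from patients who stopped, and the withdrawal rule generally ends collection before that value exists.

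Three things are at stake. First, a mixed model under missing-at-random projects the later course of withdrawn patients largely from those who stayed. If stopping the drug changes the course, the estimate moves towards the effect had nobody stopped and away from the effect in everyone randomised. Second, if stopping is more frequent on one arm, the error need not cancel. Third, removal for non-compliance or protocol violation takes out the very patients that an ITT analysis exists to keep, although section 3.6 already provides a per-protocol set to deal with deviations.

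This is a rule about data collection. The SAP can model or impute, but it cannot supply the missing observations.

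**Working it through.** **1. The rules side by side.** Suppose the last dose is at week *t*. The only later visit is then at week *t* + 4.

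- Last dose at Week 18: the visit falls at Week 22, and there is nothing at Week 24 or 36.
- Last dose near Week 32: the visit falls near Week 36 and can stand in for the primary value.
- Any materially earlier last dose leaves no Week 36 value. Values recorded before withdrawal still enter the mixed model; what is lost is the later course.

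**2. The plan's own figures.** Section 2.4 gives a difference of 7, an SD printed as 8% (read here as 8 points), 2:1 allocation, 90% power, 5% significance (two-sided by section 3.6), 20% dropout and 90 patients (60:30).

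- Placebo arm, normal formula: (1 + 1/2) × (1.960 + 1.282)² × 8²/7² = 20.6, so 21. The total is 21 + 42 = 63.
- With 20% dropout: 63/0.8 = 78.75, so 79 (81 if each arm is rounded up). A t-test calculation gives 83 to 84.
- The stated 90 is not reproduced from the stated inputs. That is a separate matter, and nothing below depends on it.
- Planned dropout: 0.20 × 90 = 18 patients, leaving 48:24. The article does not say how many of the 18 would leave through the mandatory rule.

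**3. Size of the bias, by assumption.** The article gives no withdrawal rate by arm and no course after stopping. Let *w* be the share of active patients who stop at week *t*. Let benefit accrue linearly to 7 points at Week 36, and let a fraction *f* of the benefit still to come be lost. Stopping placebo is taken to cost nothing.

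- Benefit still to come at week *t*: 7 × (36 − *t*)/36.
- Overstatement by a missing-at-random model: *w* × *f* × 7 × (36 − *t*)/36.

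Overstatement in points, for *f* = 0.5 to *f* = 1:

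| Share stopping | Week 0 | Week 18 | Week 24 |
|---|---|---|---|
| 10% | 0.35 to 0.70 | 0.18 to 0.35 | 0.12 to 0.23 |
| 20% | 0.70 to 1.40 | 0.35 to 0.70 | 0.23 to 0.47 |
| 30% | 1.05 to 2.10 | 0.53 to 1.05 | 0.35 to 0.70 |

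For 20% stopping at Week 18, the benefit still to come is 3.5 points. So 0.20 × 0.5 × 3.5 = 0.35 and 0.20 × 1 × 3.5 = 0.70. The all-randomised difference would be 6.65 to 6.3 when the on-drug difference is 7.

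**4. Scale.** With 48:24 assessed, the standard error is 8 × √(1/48 + 1/24) = 2.0 points. The Week 18 figures are therefore 0.18 to 0.35 of a standard error.

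**5. When the bias vanishes.** If patients who leave worsen unseen by *g* points, the bias is (*w* active − *w* placebo) × *g*. With 20% lost on each arm and the same *g*, it is zero.

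**The case against.** The strongest reply is that the article condenses protocol version 3.0, its schedule table is not visible here, and missing data are left to the SAP. A SAP can examine departures from missing-at-random, and it may say how the off-drug early termination score is used. All of that stands, but none of it replaces a Week 36 score that the stated rule stops collecting. It is also true that section 3.6 names the ITT set for the secondary endpoints and not for the primary one. ITT for the primary analysis is the natural reading, and the point relies on it.

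A reader might infer four stronger things that the document does not support.

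- **That losses are higher on Tecfidera.** This is plausible, since several criteria concern drug safety. But no rates are given, causality is judged by blinded sites, and pregnancy, non-compliance and protocol violation are not specific to an arm.
- **That the bias is 0.7 to 1.4 points at 20% stopping.** That holds only if those patients stop at the start, with the whole 7 points still to lose.
- **That retaining patients raises power.** Holding an assumed effect of 5 points fixed, non-central t power goes from 69% (48:24) to 79% (60:30). The same patients may dilute the effect: cut by 10% or 20%, to 4.5 or 4.0 points, power at 60:30 is 70% or 60%. At the planned 7 points it is 93% with 48:24, against 94% or 87% with 60:30 at 6.3 or 5.6 points. Recovering all 18 dropouts is also unrealistic, because patients may leave freely or die. The mixed model already uses dropouts' earlier visits.
- **That death and tracheostomy are not ascertained after withdrawal.** No section says so. The article is silent, and silence is not a prohibition.

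**Conclusion.** The point holds as a conflict between a stated follow-up rule and a stated analysis set. Mandatory withdrawal from the study, followed by one visit timed from the last dose, generally leaves these randomised patients without the Week 36 ALSFRS-R that an all-randomised comparison needs.

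The size is unknown. The illustrative 0.35 to 0.7 points rests on 20% of active patients stopping at Week 18, linear accrual to 7 points, loss of half to all of what remains, no cost of stopping placebo, and a missing-at-random model. It is smaller for later stopping, larger for earlier stopping, and zero if losses and their consequences are equal across arms. No gain in power is claimed.

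This should be fixed; confidence is moderate. It weakens what the Week 36 estimate means, but under mild assumptions it is modest against a standard error of about 2 points.

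**What to change.** Leave every clinical reason for stopping study drug as written; those criteria are not judged here. Change only what happens to follow-up:

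- State separately when study drug is stopped and when a patient leaves the study.
- After the drug is stopped, keep patients who still consent on the existing Week 12, 24, 36 and 40 ALSFRS-R assessments, by telephone where a visit is not possible.
- Do not end follow-up for compliance failure or protocol violation; the per-protocol set already handles these in analysis.
- Include values collected after discontinuation in the ITT analysis, and name ITT as the population for the primary endpoint.
- State that death or tracheostomy is ascertained for all randomised patients.

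The cost is a protocol amendment and some extra follow-up work; the article gives no budget from which to price it. Section 6 describes the trial as ongoing since October 2017, so an amendment would leave mixed follow-up rules: patients already withdrawn under the old rule may not be recoverable and should be reported as such. The ITT estimate may also come out smaller than the on-drug one.

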### Statistical methods

3.6

The statistical analysis will be performed using statistical analysis system (SAS) Version 9.4. All details regarding the statistical analysis and the preparation of tables, listings, and figures will be described in the Statistical Analysis Plan (SAP) and approved by the Sponsor before database lock. The default summary statistics for continuous variables include number of contributing observations (n), mean, SD, median, minimum, and maximum. For categorical variables, the number and percentage (in each category will be the default summary presentation. “Baseline” is defined as the last observed value of the parameter of interest prior to the first intake of IP (this includes unscheduled visits). For numerical variables, change from Baseline will be calculated as the difference between the value of interest and the corresponding Baseline value. All formal statistical tests will be two-sided at the 5% significance level. Point estimates of treatment differences will be accompanied with a two-sided 95% confidence intervals. In the case of normality assumption violations, appropriate non-parametric methods will be used for analysis. All data will be presented in by-patient listings.

The following analysis populations will be defined as follows:

i.*Intent-to-Treat (ITT) Population*- The ITT population will include all randomized patients. In this population, treatment will be assigned based upon the treatment arm to which patients were randomized regardless of which treatment they received;ii.*Safety Population (SAF)*- The SAF includes patients who are randomized and took at least 1 dose of the IP. The safety analysis will be conducted according to the treatment that a patient actually receives;iii.*Per Protocol Population (PP)-* The PP population will include all patients who do not have major protocol deviations that would affect the evaluation of the primary efficacy endpoint.

The primary endpoint (ALSFRS-R change at 36 weeks) will be analyzed using Mixed Model for Repeated Measures with treatment as fixed effect and Baseline ALSFRFS-R score as covariate. For the active treatment versus placebo comparison, the results will be presented in terms of an estimated treatment difference together with its associated 95% confidence intervals and 2-sided *P* value. Possible effects of other covariates will also be investigated. Missing data handling and possible sensitivity analysis will be described in the SAP. Details of specific alternative statistical methods in the event model assumptions are violated will be documented in the SAP.

Efficacy analysis for secondary endpoints (see outcome measures section) will be summarized and evaluated using the ITT population. Safety analyses will be performed using SAF. All safety data will be provided in by-patient listings. The safety variables that will be analyzed are outlined in Table 1. No interim analysis is planned for the study. All statistical analysis has been performed by the IQUVIA (CRO) biostatisticians in consultation with the PIs ([name] and [name]).

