### Patient enrolment and withdrawal

2.4

*Sample size calculation*: Based on previous clinical studies and literature,^[44,45]^ it was assumed that the mean difference in the ASLFRS-R score between active and placebo group at 36 weeks will be 7 [common standard deviation of 8%]. A clinically important response rate on Tecfidera was defined as 0.9, and with a 2:1 (Tecfidera:Placebo) allocation, 90% power, 5% statistical significance rate and 20% dropout rate, we estimated that 90 patients (60:30) need to be randomized inorder to attain the primary outcome measure. The inclusion and exclusion criteria are outlined in Table 2.

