### Screening Visit (Visit 1) -14 days

3.1

Patients will be screened for the study after signing an approved Informed Consent Form (ICF). As part of the screening, patient's extensive medical and neurological history will be recorded. Inclusion/exclusion criteria will be evaluated and the vital signs (blood pressure, pulse, temperature, and respiratory rate) will be recorded. Physical and neurological examinations will be performed. Patient's height and weight will be measured and body mass index (BMI) will be calculated. The visit will also involve an initial assessment of ALSFRS-R, NPI and SI, FVC as measured by handheld spirometer, SNIP test, quantitative hand muscle testing by dynamometry, and global strength using MRC score. Prior/ongoing medications will be recorded. All patients will undergo laboratory evaluation of hematological and biochemical parameters; hepatitis B, C, and human immunodeficiency virus (HIV) serology; and urinalysis. In addition, women of childbearing potential will undergo a urine pregnancy test. Urine will also be collected for neurotrophin receptor P75 levels (secondary outcome). An ALSSQOL-R questionnaire will be completed by the patient at screening.

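### The primary model names baseline ALSFRS-R as its only covariate; adding pre-baseline progression rate, computable without new data, would probably give a modest gain in precision

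*Protocol article*

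**What the plan says.** Section 3.6 (Statistical methods) specifies the primary mixed model for repeated measures "with treatment as fixed effect and Baseline ALSFRFS-R score as covariate". No other covariate is named. The section then states: "Possible effects of other covariates will also be investigated". It also says that "All details regarding the statistical analysis and the preparation of tables, listings, and figures will be described in the Statistical Analysis Plan (SAP"), to be approved before database lock. That document is not shown.

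The ingredients of a pre-baseline progression rate appear elsewhere in the article. Section 2.2 gives ALSFRS-R a maximum of 48 and schedules it at screening and baseline. Section 2.3 measures survival in months from symptom onset. Section 3.1 says that at screening the patient's "extensive medical and neurological history will be recorded". Progression rate itself is nowhere named as a variable or a covariate.

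**The concern.** The trial asks whether treatment slows progression. The current score does not separate a patient who lost a given number of points quickly from one who lost the same number slowly. The time taken to reach the score carries that information, and the primary model does not use it.

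If pre-study rate predicts Week 36 change beyond what baseline score predicts, a model that includes it has smaller residual variance, a narrower confidence interval and more power. It also adjusts for whatever imbalance in fast and slow progressors the randomisation happened to produce. Investigating covariates alongside the primary model does neither for the primary estimate. What is at stake is efficiency. The stated analysis would not give a wrong answer.

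**Working it through.** **Inputs from the documents.** All but the last come from section 2.4.
- Effect: a Week 36 difference of 7 ALSFRS-R points.
- Spread: "common standard deviation of 8", printed with a percent sign and read here as 8 points.
- Design: "with a 2:1 (Tecfidera:Placebo) allocation, 90% power, 5% statistical significance rate and 20% dropout rate".
- Planned total: 90 (60:30).
- Section 3.6: two-sided tests at 5%.

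**Inputs assumed.**
- r, the partial correlation of pre-baseline rate with Week 36 change given baseline score. The documents give none; the range 0.1 to 0.5 is shown.
- SD 8 is the residual SD after baseline adjustment. Section 2.4 does not say whether it is.
- A 5-point effect, for sensitivity only. The trial is designed for 7.

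**Step 1: the plan's own figure.** Normal approximation, 2:1 allocation: control n = 1.5 × (8 × (1.960 + 1.282)/7)² = 20.6, so 21, with 42 active, 63 evaluable. With 20% dropout, 63/0.8 = 78.75, so 79. With the t distribution, 22:44 = 66 evaluable and 66/0.8 = 82.5, so 83 (84 at exact 2:1). The stated 90 is not reproduced, but it errs on the safe side. The sample-size text also says "A clinically important response rate on Tecfidera was defined as 0.9", which has no role in a comparison of means. The present point does not depend on how 90 was reached. It uses only what 90 leaves: 90 × 0.8 = 72 evaluable, 48:24.

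**Step 2: effect of the added covariate.**
- Residual SD = 8 × √(1 − r²).
- SE = residual SD × √(1/24 + 1/48) = residual SD × 0.25.
- 95% half-width = 1.96 × SE.
- Power from the non-central t distribution.

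| r | Fall in variance | Residual SD | SE | Half-width | Power, 7 points | Power, 5 points (assumed) |
|---|---|---|---|---|---|---|
| 0 | 0% | 8.00 | 2.00 | 3.92 | 93.2% | 69.3% |
| 0.1 | 1% | 7.96 | 1.99 | 3.90 | 93.4% | 69.8% |
| 0.2 | 4% | 7.84 | 1.96 | 3.84 | 94.1% | 71.1% |
| 0.3 | 9% | 7.63 | 1.91 | 3.74 | 95.1% | 73.4% |
| 0.4 | 16% | 7.33 | 1.83 | 3.59 | 96.5% | 76.7% |
| 0.5 | 25% | 6.93 | 1.73 | 3.39 | 97.9% | 81.2% |

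As information, 72/(1 − r²) at r = 0.3, 0.4 and 0.5 is 79, 86 and 96 evaluable patients.

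**Step 3: what the covariate costs.** Estimating one more coefficient inflates the variance by about 68/67. The net factor is (1 − r²) × 68/67, which equals 1 when r = √(1/68) = 0.12. The table does not charge this inflation, so the r = 0.1 row is in practice no gain (0.99 × 68/67 = 1.005).

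**Step 4: chance imbalance.** At 60:30, the SD of the between-arm difference in a standardised covariate is √(1/60 + 1/30) = 0.224. A gap of 0.25 SD or more in either direction (0.25/0.224 = 1.12 standard errors) arises in about 26% of trials. At r = 0.4 such a gap moves the Week 36 contrast by 0.25 × 0.4 × 8 = 0.8 points.

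**The case against.** The strongest case against is that nothing here is wrong. A repeated-measures model adjusted for baseline is valid under randomisation, chance imbalance causes no bias, and the reported standard error and interval already allow for it. Analysis detail is sent to a SAP that may name further covariates. All of this stands, and it is why the point concerns a stated choice that could be better, not an omission or an error.

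A reader might infer that covariates will be chosen post hoc, leaving the primary result open to the analyst's choice. The article does not support this. It announces the investigation in advance, in addition to a specified primary model, and section 3.2 says that unblinding follows data analysis.

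A reader might also infer that the gain is certain and free. It is neither:
- The correlation is assumed throughout.
- The numerator of the rate is 48 minus a score already in the model, so only time since onset is new information.
- Recording of the onset date is inferred from the survival definition and the screening history. The eligibility and schedule tables are not shown, and a limit on disease duration, if there is one, would narrow the spread of the covariate.
- Onset dates are recalled and may be imprecise or missing.

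Finally, the larger power gains belong to a 5-point effect that the protocol does not use. At its own 7 points, power is already about 93%. These objections reduce the point's weight but do not remove it.

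**Conclusion.** The point holds as an optional, inexpensive improvement. The single-covariate model is sound but probably gives up precision that data the trial needs anyway could supply. For correlations of 0.3 to 0.5, power at the design difference rises by about 2 to 5 percentage points, and the interval half-width shrinks from 3.92 to between 3.74 and 3.39 points. At 0.2 the gain is about 1 point of power, and below about 0.12 there is essentially none. A smaller true effect would make the gain larger: about 4 to 12 points of power at 5 points for the same correlations.

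The conclusion rests on an assumed correlation, on SD 8 being in points and already net of baseline, on 20% dropout leaving 48:24, and on an onset date being available. A reader might go further and call the primary analysis biased or underpowered for want of this covariate. The documents support neither: randomisation protects the estimate, and the planned size exceeds what the stated inputs require.

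**What to change.** Before unblinding, name the primary model's covariates as baseline ALSFRS-R and pre-baseline progression rate, each by visit. Define the rate as (48 − baseline ALSFRS-R) divided by months from symptom onset to baseline, log-transformed if skewed. Because a baseline score of 48 gives a rate of zero, a log scale needs a stated convention for that case. State a rule for missing or partial onset dates. Keep the baseline-only model as a labelled sensitivity analysis and describe any other covariate as exploratory. If the SAP already does this, align the protocol sentence with it.

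The cost is a short edit to the protocol and SAP, one degree of freedom per visit, and some recall error in onset dates. No additional visits, patients or measurements are needed, provided that the onset date is captured for the survival endpoint.
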